### Study Design

A controlled feeding study with a crossover design will compare the accuracy of 3 technology-assisted methods of assessing 1 day of dietary intake: ASA24, Intake24, and mFR24. The sequence of the 3 dietary assessment periods will be randomized for each participant, with a 1-week washout period between each feeding session (Figure 1). Therefore, each participant will be exposed to each of the 3 methods at different periods. The crossover design, a repeated measurement design, will allow both between-group and within-group method comparisons. This design yields a more efficient comparison of treatments than a parallel design because fewer participants are required in the crossover design to attain the same level of statistical power or precision as a parallel design.

**Figure 1 figure1:**
[figure not shown]
Accuracy, acceptability, and cost-effectiveness of technology-assisted dietary assessment study flowchart on enrollment, randomization, and study design. ASA24: Automated Self-Administered Dietary Assessment Tool; mFR24: Image-Assisted mobile Food Record 24-Hour Recall.

Ethics approval from the Curtin University Human Research Ethics Office has been obtained (approval number: HRE2019-0222). Reciprocal ethics approval from the Department of Health Western Australia Human Research Ethics Committee has also been obtained (approval number: 201909.06), and the trial is registered with the Australian New Zealand Clinical Trials Registry (ACTRN12621000209897). All research design, practices, and reporting of studies conducted in Australia will be aligned with the Australian Code for the Responsible Conduct of Research. Participants will receive a maximum of Aus $60 (US $42) as a token of appreciation for their involvement in the study.

### Research Study Database

A purpose-built research study database will be developed using a database platform (Microsoft Office Professional Plus 2016, Microsoft Pty. Ltd) to manage, contact, and track the progress of the study participants throughout the study. The database will send autogenerated emails containing study information and personalized links to remind participants of upcoming appointments and complete applicable surveys beforehand. Email and SMS text messaging prompts will be sent directly from the study database using *Email to SMS* technology. The study database will automatically update the participant status with respect to their study compliance. The system will prompt reminders via email and SMS text messaging for participants who have not yet completed their tasks.

### Randomization

At the first face-to-face session, eligible participants will be randomized using a random number generator and stratified by gender. The order in which the participant completes the three 24HR methods will be randomly allocated to ensure no order effect. Allocation will be concealed using sealed opaque envelopes. A statistician, not involved in data collection, will generate the randomization sequence. This will ensure adequate allocation concealment from the research team involved in recruitment and data collection.

### Procedures

Each participant will complete a web-based screening and provide informed consent. If eligible, they will be directed to complete web-based baseline demographic and psychosocial surveys (taking approximately 30 minutes) and cognitive tests (taking approximately 20 minutes) before attending 3 feeding days at the Curtin University School of Population Health food laboratory. Demographic characteristics, including age, gender, and highest education attainment will be recorded. Physical activity levels will be assessed using the International Physical Activity Questionnaire, short form 7-day self-administered format [49]. Table 1 presents a brief description of the questionnaires and the tests. Figure 2 shows a conceptual framework of the role of demographic, psychosocial, cognitive, and dietary factors in misreporting, synthesized from previous literature and adapted from existing frameworks [8,36,37,39,50-52].

**Figure 2 figure2:**
[figure not shown]
Conceptual framework for assessment of factors that may be associated with 24-hour dietary recall reporting accuracy. 24HR: 24-hour dietary recall.

**Table 1 table1:** Baseline study questionnaire and test descriptions in Accuracy and Cost-effectiveness in Technology-Assisted Dietary Assessment.

Questionnaires and tests			Description of content		Study
Demographic and personal characteristics			11 items: gender, age, educational level, employment, country of birth, ethnicity, smoking, alcohol use, and socioeconomic and financial status		—^a^
Physical activity			8 items: International Physical Activity Questionnaire (short form)		[49]
**Psychosocial measures**					
	Three-factor eating	51 items measuring factors associated with eating behavior: cognitive restraint of eating, disinhibition, and hunger		[53,54]	
	Social desirability	13 items: true-false statements measuring social approval and acceptance		[55]	
	Fear of negative evaluation	12 items: 5-point scales to assess concern about being perceived unfavorably by others		[56]	
	Time pressure	7 items: assesses the competing perceived time pressure		[57]	
	Perceived Stress Scale	5 items: assesses perception of external environmental stressors; short version of the original Perceived Stress Scale-14		[58]	
	Weight loss history	2 items: assesses frequency and magnitude of previous weight loss.		[59]	
**Cognitive measures**					
	Visual digit span (forward and backward)	Assesses working memory by asking participants to recall spans of digits in 14 trials. Participants will see digit sequences on a computer or mobile phone screen and must recall them by selecting the recalled digits from a circle of digits with the mouse or their finger.		[60]	
	Vividness of visual imagery questionnaire	16 items: 5-point scale administered twice to assess conceptualization of visual memory. Participants imagine people and scenes and rate the vividness of these mental images (first with eyes open and then with eyes closed).		[61]	
	Trail making test	Assesses visual attention and task switching. Participants are asked to draw lines in specific, predetermined sequences from node to node on a screen as quickly and as accurately as possible.		[62]	
	Wisconsin card sorting test	Assesses cognitive flexibility and executive function. Participants are asked to sort cards into 4 different “categories.” No instructions are given regarding the categorization rules. Participants are informed whether each selection was correct or incorrect. The cards to sort into these piles have similar designs and vary in color (4 variants), shape (4 variants), and number of shapes (4 variants). Categorization rules change midtask without warning.		[63]	

^a^Question items devised by authors.

### Feeding Days

The participants will attend the food laboratory on 3 separate days. On day 1, they will receive a brief introduction to the study (with the objective described as finding better ways to assess what people eat) and be randomized. They will have their height and weight measured using standard protocols [64]. At the food laboratory, participants will consume 3 meals ad libitum (breakfast, lunch, and dinner) on the same day and will leave the laboratory between meals. No restrictions will be placed on consuming food and beverages outside of the laboratory meals. The participants will select from a menu and will not have access to the weight of their food and beverage selections. Menu items will be selected based on a combination of the top 100 most commonly consumed meals and snacks in Australia (Australian Bureau of Statistics, personal communication, 2020).

Each participant will enter the food laboratory one at a time to consume their meal. In accordance with the COVID-19 protocols issued by the Western Australia Government Department of Health, participants will be separated by screens and physically distanced from each other, with a maximum of 8 participants at any one time. This may change if restrictions are eased. All food and beverage items will be inconspicuously weighed using Kelba KHX-3 bench scales (Kelba) with a 0.1-gram resolution in a separate laboratory space before being served on the participant tray. Before delivering the tray to each participant, the researcher will inconspicuously take an image of the tray using a researcher version of the mFR24 app that allows insertion of a unique user ID for each image. When finished eating, each participant’s tray will be collected and an *after image* with the researcher mFR app will be taken. Plate waste will then be weighed to determine the amount of each item consumed. The amount consumed will be determined by subtracting the weight of the food plate waste from the weight of the served amount. Weighing will be conducted in duplicate, and a third measure will be taken if the first 2 measures differ by >0.5 grams. The average of the 2 closest measures will be recorded.

### 24-Hour Dietary Recall Interview Methods

Each day subsequent to the feeding day, the participants will complete a 24HR interview remotely, each time via a different technology-assisted dietary assessment method (ASA24, Intake24, or mFR24), the order of which will be randomized.

#### Automated Self-Administered Dietary Assessment Tool (2016)

Participants will be emailed a weblink and a username and password to access the ASA24 interface. A consortium of Australian Universities adapted the ASA24 by incorporating Australian food composition tables [65]. Participants will be asked to (1) report everything they had to eat and drink the previous day from midnight to midnight by selecting an eating occasion and time, then searching for matching food and beverage items, and reviewing any gaps in consumption of more hours; the database contains >4800 foods and beverages from Australian food composition tables (AUSNUT 2011-2013); (2) provide additional details of each food and beverage item (eg, form, preparation method, additions, and amount consumed); food images in ASA24 will assist in portion size estimation; (3) review and edit all the foods and beverages they selected; (4) add any commonly forgotten foods and beverages that they consumed after being prompted and directed back to the food list; and (5) confirm that they have recorded all of the food and beverages from the previous day [13]. Participants can add food and beverages that are not in the database via a *missing foods* tool incorporated in a bespoke spelling correction system to address misspelled food names. In previous studies, participants completed the ASA24 in 17 to 34 minutes [66].

#### Intake24

Participants will be emailed a weblink to access the Intake24 interface. A short instructional video is provided for the participants to watch before commencing the 24HR interview. Participants will be asked to (1) key in all the foods and beverages consumed the previous day between waking up and going to sleep as free text; (2) select items from a database and match each item consumed; the database contains >2800 foods and beverages by incorporating Australian food composition tables (AUSNUT 2011-2013) [67]; participants will be able to add food and beverages not included in the database via a *missing foods* tool incorporated in a bespoke spelling correction system to address misspelled food names; participants can add their own personal recipes, sandwiches, and salads; (3) estimate the portion sizes of the items consumed using images and standard serving sizes; (4) review all the foods and beverages they have selected and edit if necessary; and (5) add any missing items associated with the foods they have already selected after being prompted to do so [12]. Previous studies indicate an average completion time of 20 minutes.

#### Image-Assisted Mobile Food Record 24-Hour Recall

#### Overview

The mFR24 app, an image-based dietary assessment system [20,22,23,68], will be adapted as an image-assisted 24HR method for this study. The system consists of a mobile food record app (mFR24), which runs on a mobile device (iPhone or Android smartphone) and a dedicated cloud-based server for the storage of images, metadata, and food image processing and analysis. Using the mFR24, participants will take pictures of their food and beverages before and after eating. The images will be automatically uploaded to the cloud-based server via Wi-Fi or the 4G or 5G network. The content of the images will then be confirmed by the participant in a process known as user confirmation. A researcher version and a participant version of the app will be used in this study. The researcher version will be installed on various devices and used to take before and after images of each participant tray. These images will be uploaded to a researcher folder on the server. The participant version of the app will include additional features.

When allocated to the mFR24, the participants will install the mFR24 (participant version) on their smartphones and be shown how to use the mFR24 app on the feeding day by a research assistant. They will be instructed to take a *before* and *after* image of all meals, beverages, and snacks consumed from the first meal served at the study center until midnight and include a fiducial marker (a colorful checked object of known size, color, and shape that assists in food and beverage recognition and quantification) in each image. mFR24 has an automated feature to detect the presence of the fiducial marker and alert participants if the fiducial marker is missing from the image. An angle-detection algorithm assists participants in taking the image at the correct angle (between 45° and 60° from the horizontal plane). Once captured and confirmed by the participant, the images will no longer be accessible to the participant until the user confirmation step (Figure 3). At the dinner session, participants will receive training on how to label their images for user confirmation the following day.

**Figure 3 figure3:**
[figure not shown]
Screenshots of the mFR24 application interface showing the steps in the review process and viewing an eating occasion. (a) image list with time and date stamp displayed (b) viewing a labeled eating occasion with colored pins and labels identifying the food and beverages. The image also shows the inclusion of the fiducial marker.

#### User Confirmation

The mFR24 app includes a feature known as the *user confirmation step*, where once midnight has lapsed, the images are returned to the participant for labeling with food and beverage names. On the day following the feeding day, participants will select and label each image from the review function in the mFR24 app (Figure 3). To label a food or beverage, the participant will tap on the item, and a pin will appear with *tap to edit*. Tapping the pin again will take the participant to the food list *search function*. When the participant starts typing the word, a list of foods will appear where they can select from the list. The food list consists of 372 food and beverage items. The food list has been adapted so that a *mini label* and *short description* are displayed to the participant. These labels link to a food composition database (not visible to the participant) with the food code, detailed description, and energy and nutrient composition (AUSNUT 2011-2013 nutrient database). If the participant cannot locate their food item in the list, typing *food not listed* will allow a free text entry. Once confirmed, the image with the confirmed pins is automatically sent to the server and disappears from the app. Participants will be asked to complete this task before the mFR24 interview. Researchers will be able to view the participant’s annotated images on a secure server.

#### mFR24 Interview

A trained researcher will conduct a 24HR interview following an adapted multiple-pass approach [69] outlined in Table 2. This 24HR process will enable the estimation of the total intake of food and beverages consumed during a 24-hour period. The recall process will be assisted by the labeled food and beverage images taken by the participant using the mFR24 app. The interview will be conducted via a video call on the day following the controlled feeding day. The interview structure is based on the AMPM developed by the United States Department of Agriculture [10]. Briefly, the original 5 steps include the collection of a quick list of foods and beverages consumed, a check for commonly forgotten foods, time and occasion, details and review, and a final probe. In the adapted version used in this study, the quick list and time pass will be completed by researchers before the interview using the participant labeled images, which will be viewed on a secure server.

**Table 2 table2:** Adaptations of the United States Department of Agriculture Automated Multiple-Pass Method in the interview structure for the Image-Assisted mobile Food Record 24-Hour Recall interview.

Automated Multiple-Pass Method steps	Aim	Image-Assisted mobile Food Record 24-Hour Recall steps	
		When image is taken	When image is not taken
Step 1: quick list	The purpose of the quick list pass is to obtain a quick report of foods and beverages consumed in the past 24 hours without interrupting the respondent and to introduce the respondent to the concept of 24-hour recall.	Taken from the mini label and image provided by the participant; participant is asked to list any foods and beverages consumed that are not shown in images.	Participant is asked to list all foods and beverages consumed that are not shown in images.
Step 2: forgotten foods list and additions	The forgotten foods list prompts the respondent’s memory and collects other foods or beverages that are not reported in the quick list.	Participants are asked if they consumed items from a list of commonly forgotten foods.	Participants are asked if they consumed items from a list of commonly forgotten foods.
Step 3: time and occasion	The time and occasion of food or beverages consumed are recorded.	This does not require a separate pass. Time of eating is taken from the image metadata.	Ask participant to recall time and occasion of forgotten foods when item is reported.
Step 4: detail cycle	The aim of this step is to collect specific descriptive information about each food item and beverage reported and record quantities and any additions made to the food.	Clarify only nonidentifiable food and beverage items; follow the Australian Health Survey food model booklet to confirm amounts consumed; and check the after image for leftovers.	Use food-specific probes to obtain details; follow the Australian Health Survey food model booklet to confirm amounts consumed; and probe leftovers.
Step 5: final probe	This is the last opportunity for the respondent to remember any new foods and beverages.	Read out the list of food and beverage items.	Read out the list of food and beverage items.

The video call interview will consist of a quick list of any foods or beverages for which an image was not taken, a probe for commonly forgotten foods, a detail cycle, and a final probe. The researcher will use a screen-sharing function to enable both the researcher and participant to view each image simultaneously. During the detail cycle, participants will be asked to provide food and beverage details when these are unclear from the images. The participants will also be asked to describe the amount of each item consumed, using the standard food model booklet used in the Australian Health Survey [70]. Household measures such as metric teaspoons or pieces will also be used to describe amounts not available in the booklet and may, in some instances, be the preferred method of portion size description by the participants. During the final probe, the researcher will confirm all foods and beverages, descriptions, and portion sizes reported by the participant. The researcher conducting the 24HR interviews will not have access to the observed intake data and will not be present on the feeding day. Following the interview, data will be entered into a nutrition analysis software (FoodWorks 10, Xyris Software) linked to the AUSNUT 2011-2013 nutrient database to estimate food, energy, and nutrient intake for the 24-hour recall period.

#### Automated Image Analysis

Automated methods using computer vision and machine learning (eg, deep learning) techniques will also be undertaken [21-23] using the images collected with the mFR24. The study will test the accuracy of automated methods using computer vision and machine learning techniques to estimate true intake. These methods include food identification [71], food segmentation [72], and volume estimation (for food portion size estimation) [73]. In recent years, there has been rapid proliferation in the use of artificial intelligence and machine learning techniques in image analysis, particularly the use of deep learning methods based on neural networks [74]. The authors ([name] and FZ) from Purdue University have recently developed several deep neural network approaches for food image analysis and will modify these methods for use in this study. This will include generating ground truth images to train the deep neural networks using a series of standard images of the food and beverage items to be served at each meal with known food weights. As deep learning methods require a large amount of training data, we will investigate the use of data augmentation methods, particularly using generative adversarial networks [75], to aid in training. Trained models will then be used to recognize the food types, estimate the food portions, and compare the automated methods with the true intake. Standard metrics of precision and recall will be used in the computer vision and machine learning fields to determine the performance of the automated techniques.

### Poststudy Acceptability Questionnaire

The participant’s perceptions of the acceptability of the 24HR method will be asked at the end of the study via a web-based survey using both open and closed questions. Their perceptions of each method will be asked about one at a time in a randomized order. Participants will be asked what device they used to complete each method and then be asked questions using a 5-point Likert scale to rate their agreement with statements including how easy it was to find and remember foods and remember amounts and whether they would be willing to use the method again. Open-ended questions will explore the participant’s likes and dislikes about each method. Finally, participants will be asked which of the methods, if any, they preferred and why.

### Exit Interviews

A qualitative methodological approach using in-depth interviews and reflexive thematic analysis [76] will explore and describe perceptions and beliefs regarding each of the dietary assessment methods. Approximately 10% (20/150) of the recruited sample (participants stratified by age and gender) will be invited to participate in a semistructured in-depth interview. The script will include questions regarding what would motivate participants to take part in studies assessing dietary intake, barriers and enablers to participation, retention, and most-favored incentives to diet research participation (eg, dietary feedback and financial incentives). Questions will also be asked about the acceptability of the mFR24 method and features (eg, labeling of images). Interviews will be audio-recorded, transcribed verbatim, and reviewed for accuracy by the participant and researcher before analysis. Transcripts will be managed using transcription software (NVivo 12.6, QSR International). Sampling and analysis will continue until pragmatic saturation is reached [76].

### Cost and Cost-effectiveness of Measures

Both financial and time costs for participants to use each of the methods will be assessed. The time spent by researchers and participants in the administration of each 24HR method will be recorded for each participant. This includes time spent training individuals to take the mFR24 images, time spent completing the 24HR interview, and any time spent supporting individuals to complete their 24HR interviews. The time spent by researchers coding the mFR24 data will also be recorded. Both ASA24 and Intake24 have the capability to collect time stamp data to identify how much time the participants spend inputting data. All other time data, including time spent cleaning the data, will be manually collected by researchers.

Financial costs, such as server space for digital data storage, will be recorded. After converting the time data to a financial cost, the total cost data will be considered in parallel with the measures of accuracy derived for the 3 methods. The primary accuracy measure for cost-effectiveness is the absolute percentage error in energy intake. Comparing costs with accuracy will identify whether any of the 3 methods are dominated by another (ie, is more expensive and less accurate). If not, the cost per person to reduce absolute misreporting by 1% point will be estimated.

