### Data Analyses

#### Energy Intake Estimation Accuracy

The participant feeding days with at least two meals eaten at the food laboratory will be included in the analyses. Daily energy intake from each 24HR method and the controlled feeding sessions will be calculated, excluding any items reportedly consumed outside of the food laboratory. Outlier checks will be conducted to identify any obvious keying errors or food composition data anomalies, which will be corrected before proceeding. Bland-Altman plots will be used to test for agreement between the 24HR values and controlled feeding measures at the individual and group levels. Repeated measurements will be analyzed using the linear mixed models procedure using SPSS version 25, accounting for age, gender, and BMI, with 24HR method and method order as fixed effects, to assess whether there are statistically significant differences by 24HR method. Misreporting will be assessed by examining the ratio of reported 24HR intake to observed intake, with the lowest tertile considered to indicate underreporting. The proportion of underreporters in each 24HR method will be compared using chi-square tests and logistic regression. Among underreporters, the total energy misestimation will also be compared using regression models adjusted for age, gender, and BMI.

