#### Correlates of Energy Misestimation

Psychosocial, demographic, and cognitive factors associated with omission and intrusion rates and with energy misestimation on each 24HR method will be evaluated using chi-square tests and multivariate logistic regression. The effects of factors will be reported as odds ratios and associated 95% CIs. Some dietary factors in the Accuracy and Cost-effectiveness of Technology-Assisted Dietary Assessment study are standardized because of the controlled feeding methodology (meal frequency and eating location), but it is hypothesized that food and meal complexity and physical form will affect reporting accuracy via an interaction with cognitive factors. P<.05 will be considered statistically significant in all analyses.

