#### Cost-effectiveness

Both participant and researcher time costs will be multiplied by standard staff costs (including on-costs) to estimate the financial cost of using each method on a per-person basis. Differences in time cost and total financial cost will be compared across methods using a repeated measures analysis of variance test. P<.05 will be considered statistically significant. If statistically significant differences exist, differences in cost-effectiveness will be assessed using the same procedure. Cost-effectiveness will be defined as the cost per person to reduce the absolute misestimation of energy intake by 1% point.

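### The dominance comparison sets no uncertainty criterion for the accuracy half, and the cost per percentage point of error is made to depend on two different conditions

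*Protocol article*

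**What the plan says.** The Protocol article treats cost-effectiveness in two places.

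*Cost and Cost-effectiveness of Measures* fixes the accuracy scale: "The primary accuracy measure for cost-effectiveness is the absolute percentage error in energy intake". It says that "the total cost data will be considered in parallel with the measures of accuracy derived for the 3 methods", and then defines the comparison: "Comparing costs with accuracy will identify whether any of the 3 methods are dominated by another (ie, is more expensive and less accurate". The next sentence branches on the answer: "If not, the cost per person to reduce absolute misreporting by 1% point will be estimated".

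*Cost-effectiveness*, under *Data Analyses*, gives the tests. "Differences in time cost and total financial cost will be compared across methods using a repeated measures analysis of variance test", at the 5% level. Then: "If statistically significant differences exist, differences in cost-effectiveness will be assessed using the same procedure". It defines cost-effectiveness as the same cost per percentage point and does not mention dominance.

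*Energy Intake Estimation Accuracy* fits a linear mixed model to the repeated energy data "to assess whether there are statistically significant differences by 24HR method". It does not name absolute percentage error as the outcome and is not tied to the dominance comparison.

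**The concern.** Dominance needs two facts about a pair of methods: one costs more, and the same one is less accurate. The plan tests the first and states no criterion for the second. The cost condition will probably be met. The mFR24 adds participant training, a trained interviewer on a video call, data entry after the interview and coding time, none of which the self-administered tools need in the same form. Once costs differ, the direction of the accuracy difference settles dominance, and nothing stated prevents a chance difference from settling it.

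The branch adds a second problem. With three methods, one can be dominated while two remain, and the trade-off between those two is then the useful result. Read literally, the plan drops the cost per percentage point as soon as any method is dominated.

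The result is meant to help policy makers and researchers choose a method for large surveys. A method could be set aside as both dearer and less accurate when the data show no accuracy difference, or when it is in truth the more accurate one.

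**Working it through.** **Inputs.** From the article: three methods; the definition of dominance; absolute percentage error in energy as the accuracy measure; 150 randomized with 20% dropout, so 150 × 0.80 = 120 completers (*Sample and Recruitment*). The article gives no error rate for the dominance comparison, so there is no figure of its own to reproduce. It also gives no SD for absolute percentage error, so the SDs in step 4 are assumptions.

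**1. Which stated test could supply the accuracy criterion?**

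- The repeated measures analysis of variance covers time cost and total cost, then the cost-effectiveness ratio. It does not test accuracy on its own.
- The mixed model addresses energy intake by method. Over- and under-reporting cancel in a mean difference but not in an absolute error, so its result does not carry over to the measure used for dominance.
- The regression of total energy misestimation is confined to underreporters.

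None is a between-method test of absolute percentage error in all participants.

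**2. Equal accuracy, strictly ordered costs, point estimates decide.** Call the methods A (cheapest), B and C (dearest). Rank the observed mean errors, 1 being the smallest. With equal and exchangeable accuracy the six orders are equally likely.

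| Error rank A, B, C | Dominated |
|---|---|
| 1, 2, 3 | B and C |
| 1, 3, 2 | B and C |
| 2, 1, 3 | C |
| 2, 3, 1 | B |
| 3, 1, 2 | C |
| 3, 2, 1 | none |

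- P(at least one dominated) = 1 − 1/6 = 5/6 = 83.3%.
- P(C dominated) = 4/6 = 67%.
- P(exactly one dominated) = 3/6 = 50%. In these trials the literal branch loses the estimate for the remaining pair.

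Simulation with 120 completers, 20,000 runs per setting, within-person correlation 0 to 0.6 and half-normal or lognormal errors gave 83.2% to 83.5%.

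**3. How far the 83% depends on its assumptions** (point estimates still decide):

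- A and B tie exactly on cost: only C can be dominated, and it escapes only with the smallest error, so 1 − 1/3 = 67%.
- Equal mean errors, unequal SDs (ratios up to 4:1): about 78% to 90%.
- Dearer methods truly more accurate, by 1 standard error of the difference per step: 31%. By 2 standard errors: 4.5%.

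**4. A costlier method that is truly more accurate, two methods only.** P(called dominated) = Φ(−δ / (SD/√120)), where δ is its true advantage and SD is the SD of the paired difference (assumed 15, 20 or 25 points).

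- δ = 2 points: Φ(−1.46) = 7%; Φ(−1.10) = 14%; Φ(−0.88) = 19%.
- δ = 1 point: Φ(−0.73) = 23%; Φ(−0.55) = 29%; Φ(−0.44) = 33%.

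**5. Effect of an uncertainty criterion under the null of step 2.** Requiring an unadjusted pairwise difference at two-sided 0.05 in the dominated direction gives false dominance in 6.1% to 6.7% of trials. An omnibus test at 0.05 plus pairwise tests gives 2.6% to 3.0%.

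**6. The two conditions for one quantity.** One section estimates the cost per percentage point if no method is dominated. The other assesses it if costs differ significantly. If costs differ significantly and one method is dominated, the first section omits the quantity and the second goes on to analyse it.

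**The case against.** The strongest reply is that the article defines a term and does not fix a decision rule. It never says that the order of the means decides. It sets a general level ("P<.05 will be considered statistically significant in all analyses") and tests energy by method, so less accurate may be meant in the light of those tests. A condensed article may also leave uncertainty in cost-effectiveness to a fuller plan.

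Much of this stands. A reader might infer that the plan prescribes dominance from the bare ordering of means and so has an 83% error rate. The text does not support that: it is silent on the criterion and does test costs. Nor is 83% a rate of harmful choices. If accuracy is truly equal, choosing the cheaper method is right, and only the label less accurate is wrong. A reader might also take dominance to be the headline cost-effectiveness conclusion; it appears in one passage, and neither the abstract nor the *Data Analyses* paragraph mentions it.

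The branch can also be read as applying to whichever methods are not dominated.

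The reply does not remove the point. The article names the measure, defines dominance and makes a later analysis depend on it, while the test nearest to hand does not name that measure. The mismatch between the two conditions is in the text itself.

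**Conclusion.** The point holds as a gap in a stated comparison and a mismatch between two sections. Accuracy enters dominance with no uncertainty criterion, the only stated gate is on cost, and no between-method test of absolute percentage error is given. The cost per percentage point has two different conditions, and the literal wording of one drops it for a remaining pair.

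The size is conditional. The 83% requires that point estimates decide, that accuracy is equal and exchangeable, and that costs are strictly ordered. It falls to 67% if the web tools tie on cost, and to 31% or 4.5% if dearer methods are truly better by 1 or 2 standard errors per step. The more harmful error, setting aside a costlier method that is truly better, is 7% to 33% under the assumed SDs and advantages. The change should be made before analysis.

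**What to change.** In *Cost and Cost-effectiveness of Measures*:

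- For each pair of methods, estimate the paired difference in cost and in absolute percentage error in energy.
- Bootstrap participants jointly, keeping all of a participant's visits together. Report 95% CIs and the bootstrap probability of dominance next to any dominance statement.
- Describe a dearer method whose accuracy CI includes zero as *costlier, no demonstrated accuracy difference*.
- Replace the opening *If not* with *For all non-dominated methods*, so that a remaining pair keeps its estimate.

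Reconcile this condition with the cost-only gate in *Cost-effectiveness* under *Data Analyses*, so that both sections state the same one.

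No new data are needed. The cost is slightly more analysis and fewer unqualified dominance statements. Reserving the word dominated for pairs where both CIs exclude zero is one possible convention and is not essential to the fix.
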